### Sample size calculations

To account for cluster randomisation, sample size calculations were based on recent sample size requirements developed by Heo & Leon [49]. to detect intervention by time interactions in longitudinal cluster randomised clinical trials. The CSC trial will be powered to detect differences in the overall sample as well as between samples from each of four groups within the three States of NSW, QLD and WA. To allow for comparisons within each State, six schools (with at least 100 students) in each of the four intervention groups are required per state, giving a total of 24 schools per State (at least 2400 students). This achieves 80 per cent power to detect a standardized between-group mean difference of 0.15 (p = 0.05) in outcomes at the end of the trial with seven measurement occasions. An effect size of 0.15 is comparable to previous school-based trials of universal mental health and substance use prevention programs and would have substantial benefits on a population level based on recent economic modelling [50]. To account for school dropouts during the trial, which we expect to be approximately 10 per cent, we aim to recruit at least 28 schools in each State (at least 2800 students). This will result in an overall sample of 8400 students from 84 schools at baseline to test the efficacy of the CSC intervention in comparison to the other groups. Based on previous research using the *CLIMATE Schools* programs, school participation rates for similar trials were approximately 30 per cent [48,51]. Therefore, to recruit a total of 84 schools, approximately 270 schools will be approached to participate.

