#### ***Assessment occasions***

Regardless of the condition to which schools are assigned, all students will be assessed via a self-report questionnaire at; baseline, immediately pre and post each *CLIMATE Schools* program (i.e., *Substance Use* and *Mental Health* programs) and 18, 24 and 30 months after baseline. Schools will have the option to complete the assessments either online or by paper and pencil. Each student will be assigned a unique username and password to login to the study website and all survey data obtained is strictly confidential. Table 2 displays the anticipated CSC study assessment times.

**Table 2 T2:** Climate Schools Combined (CSC) study timeline

	**Survey 1**	** *Climate Schools- Substance Use (module 1)* **	** *Climate Schools – Substance Use (module 2)* **	**Survey 2**	**Survey 3**	** *Climate Schools-Mental Health* **	**Survey 4**	**Survey 5**	**Survey 6**	**Survey 7**
**Time**	**Term 1**	**Term 1**	**Term 3**	**Term 3**	**Term 1**	**Term 1**	**Term 1**	**Term 3**	**Term 1**	**Term 3**
	**2014**	**2014**	**2014**	**2014**	**2015**	**2015**	**2015**	**2015**	**2016**	**2016**
**CS-C***	✓	X	X	✓	✓	❖	✓	✓	✓	✓
**CS-SU***	✓	X	X	✓	✓		✓	✓	✓	✓
**CS-MH***	✓			✓	✓	❖	✓	✓	✓	✓
**CO***	✓			✓	✓		✓	✓	✓	✓

Key:

*CS-C = Climate Schools Combined group.

*CS-SU = Climate Schools - Substance Use intervention only group.

*CS-MH = Climate Schools - Mental Health intervention only group.

*CO = Control group.

✓ = Measurement occasion.

Χ = Climate Schools - Substance Use 12 lesson intervention.

❖ = Climate Schools - Mental Health 6 lesson intervention.

Survey time points:

Survey 1: Baseline.

Survey 2: Post-Substance Use intervention.

Survey 3: Pre-Mental Health intervention.

Survey 4: Post-Mental Health intervention.

Survey 5: 6-month follow-up.

Survey 6: 12-month follow-up.

Survey 7: 18-month follow-up.

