#### ***Statistical analysis***

Single-level analyses; one-way analyses of variance (for normally distributed data), Chi-square (for binominal data), and Mann-Whitney U-test (for non-normally distributed data) will be used to examine baseline equivalence and attrition between groups. Due to the multi-level and hierarchical nature of the data, mixed effects regression will be used to examine intervention by time interaction effects. To account for intracluster variance within States or schools, intervention effects will primarily be examined using hierarchical linear modelling (HLM) for normally distributed data and hierarchical generalized linear modelling using a Poisson distribution for count data. Outcome variables will be centred at post-test to allow for comparisons between groups immediately after the intervention, and growth terms will be analysed to determine the magnitude of the follow-up effects. Analyses will be conducted using the program Stata. If unconditional models reveal that less than 10% of systematic variance exists at the between State or between school level for any outcome variable, HLM will be abandoned and single-level analyses will be used [67]. For these variables, ANCOVAs utilising the SPSS GLM procedure will be conducted to account for any baseline differences that might exist between groups. For multiple comparisons Bonferroni adjustments will be made. Effect sizes, odds ratios and 95% confidence intervals will also be calculated.

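### A variance threshold unrelated to missing data decides, outcome by outcome, whether withdrawn students' surveys are used; on the ANCOVA route they are by default lost, and the estimate can be biased

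*Protocol article*

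**What the plan says.** All of the analysis rules are in the Statistical analysis section of the protocol article.

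- Main route: "mixed effects regression will be used to examine intervention by time interaction effects", using hierarchical linear models, or hierarchical Poisson models for counts.
- Trigger for leaving it: "If unconditional models reveal that less than 10% of systematic variance exists at the between State or between school level for any outcome variable". The models are then dropped in favour of single-level analyses.
- Fallback route: "For these variables, ANCOVAs utilising the SPSS GLM procedure will be conducted to account for any baseline differences that might exist between groups".
- Attrition: single-level tests "will be used to examine baseline equivalence and attrition between groups". That compares attrition between arms. It does not say how incomplete records enter either route.

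Two other sections matter. Under Assessment occasions, every arm is surveyed at "baseline, immediately pre and post each *CLIMATE Schools* program" and at three later follow-ups, which makes seven surveys in Table 2. Under Sample size calculations, the power claim concerns a difference "in outcomes at the end of the trial with seven measurement occasions". The only dropout figure given there is about 10% of schools; no student rate is stated.

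**The concern.** The trigger measures how much of an outcome's variance lies between States or schools. That bears on clustering and not on who is missing. The two routes nevertheless treat an incomplete record differently by default.

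Take a student who leaves after Survey 4. In the mixed model, four surveys contribute. In an ANCOVA of Survey 7 on Survey 1, none do. If depression stays on the first route and alcohol use moves to the second, this student counts for one primary outcome and not for the other. The two results then describe different students and rest on different missing-data assumptions.

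The trigger is not remote. It names the State level or the school level, so read literally a low share at either one is enough.

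At stake is the end-of-trial contrast. If the link between interim scores and leaving differs by arm, an analysis of those still present compares differently selected groups, and adjusting for baseline does not undo selection that happened later. This is distinct from ignoring clustering: school-corrected standard errors for the ANCOVA would leave it untouched.

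**Working it through.** **1. The plan's own figures.** Inputs from Sample size calculations: "six schools (with at least 100 students) in each of the four intervention groups are required per state", hence 6 × 100 = 600 students per arm per State; difference 0.15 SD; 80% power; alpha 0.05 (two-sided assumed); seven occasions.

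- Single end-point comparison, no clustering: n = 2(1.960 + 0.842)²/0.15² = 698 per arm. With 600 per arm, power is 73.8%.
- Seven-survey slope contrast: SD of the end-of-trial difference = L√[(1 − ρ)/Σ(t − t̄)²], where L is the time span and ρ the correlation between surveys. With equal spacing, L² = 36 and Σ(t − t̄)² = 28, so n = 698 × (36/28) × (1 − ρ). This equals 600 at ρ of about 0.33. With assumed months 0, 6, 12, 13, 18, 24 and 30 it needs ρ of about 0.39.
- Neither ρ nor the intracluster correlation is stated, so the 600 can be neither confirmed nor refuted. The school allowance is consistent: 24/0.9 = 26.7, rounded up to 27; the next multiple of four arms is 28; 3 × 28 = 84 schools.

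The power claim therefore describes a seven-occasion analysis, and the ANCOVA is not that analysis.

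**2. What each route uses by default.**

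| Student's record | Mixed model | ANCOVA, Survey 7 on Survey 1 |
|---|---|---|
| All seven surveys | 7 surveys | 2 surveys |
| Leaves after Survey 4 | 4 surveys | none |
| Leaves after Survey 6 | 6 surveys | none |

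If the fallback were run as a repeated-measures GLM, any student missing any survey would be deleted, which loses more.

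**3. Size of the possible bias, with a true effect of 0.15.** Assumptions, none of them from the document: 600 per arm; seven surveys; correlation 0.4 + 0.6 × 0.6^lag; students who leave do not return; no clustering; 300 replicates (Monte Carlo SE about 0.003). The log-odds of leaving rise by 0.3 (mild) or 0.6 (strong) per SD of score, in one arm only unless stated. The comparator is a sequential regression that uses all observed surveys.

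| Dropout mechanism | Lost (approx.) | ANCOVA on those present | All surveys |
|---|---|---|---|
| Completely at random | 20% | 0.146 | 0.147 |
| Baseline score, differing by arm | 21% | 0.149 | 0.151 |
| Previous score, same in both arms | 22% | 0.144 | 0.146 |
| Previous score, one arm, strong | 10% | 0.129 | 0.149 |
| Previous score, one arm, mild | 20% | 0.130 | 0.149 |
| Previous score, one arm, strong | 21% | 0.107 | 0.147 |
| Previous score, one arm, strong | 34% | 0.083 | 0.151 |
| Unseen current score, one arm | 21% | 0.090 | 0.119 |

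In the four rows with previous score in one arm, the ANCOVA shortfalls are 0.150 − 0.130 = 0.020, 0.150 − 0.129 = 0.021, 0.150 − 0.107 = 0.043 and 0.150 − 0.083 = 0.067 SD. That is 13% to 45% of 0.15.

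**4. A second simulation, with no programme effect.** It used 400,000 students per arm, surveys at months 0, 6, 12, 14, 18, 24 and 30, and about 20–27% lost, with dropout linked to the last observed score in one arm only. At an odds ratio of 1.5 per SD the ANCOVA bias was −0.025 to −0.035 SD; at 2 per SD it was −0.045 to −0.064 SD. The range is 0.025/0.15 = 17% to 0.064/0.15 = 43% of the target. The all-survey estimate stayed within 0.003 SD of zero.

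**5. Direction.** In both simulations high scorers leave one arm, which pulls that arm's mean down. On a knowledge score this hides a gain; on a symptom score it looks like a benefit. If the other arm loses them, the sign reverses.

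**The case against.** The strongest reply is that the article never says absent students are deleted. It does not name the survey the ANCOVA uses, define who is analysed, or exclude imputation, and a fuller protocol or analysis plan may settle all three. The section also stresses comparison immediately after the intervention; in an ANCOVA at Survey 4, the student who leaves after Survey 4 would be included. This stands as a limit: deletion is inferred from the procedure's default, and Survey 7 from the end-of-trial power statement. It does not remove the switch, which the article does state. The absence of a missing-data rule in a condensed article is not the point being made.

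Other parts of the reply also stand:

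- **Bias is conditional.** A reader might infer that any selective withdrawal biases these outcomes. The figures do not support that: dropout driven by baseline, or alike in both arms, did little harm.
- **Differential dropout is not shown.** A reader might infer it from 18, 12, 6 and 0 programme lessons. But controls receive usual lessons on the same topics, all arms complete the same surveys, and the article reports high follow-up in an earlier trial of the substance use programme. Its 10% loss of schools is not score-driven loss of students.
- **The comparator is not the planned model.** It is a sequential regression under a missing-at-random mechanism, not the hierarchical model with growth terms. When the unseen score drives dropout, both estimates are biased (0.090 and 0.119 against 0.15).
- **Fewer surveys need not mean less power.** Without clustering or dropout, 600 per arm gives an ANCOVA 77.7% power at a baseline correlation of 0.3 and 85.1% at 0.5. The objection is that the power statement does not describe this analysis, not that power must fall.

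Finally, the same switch has a more certain fault: it ignores clustering. At an intracluster correlation of 0.10 with 100 students per school, the design effect is 1 + 99 × 0.10 = 10.9. One edit cures both faults, but correcting the standard errors alone would cure only that one.

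**Conclusion.** The point holds in a limited form. The article fixes a rule under which a variance share unrelated to missing data decides whether an outcome is analysed with all completed surveys or, by default, only with students who have both the baseline and the outcome survey. The same withdrawn student can then count for one primary outcome and not for another, and the fallback gives up the seven occasions on which power was claimed.

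The ANCOVA estimate can be biased, in either direction, if dropout depends on interim scores differently by arm. The illustrative size is about 0.02–0.07 SD against a target of 0.15 SD, at assumed student dropout of about 10–34%. These magnitudes rest on assumed dropout rates, mechanisms and correlations, because the article gives none. The documents do not support a claim that the outcomes will be biased, that programme benefit in particular will be exaggerated, or that the mixed model is safe whatever drives dropout. The change should be made; confidence is moderate.

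**What to change.** Delete the switch to ANCOVA. For every outcome, whatever its between-school variance, keep the likelihood-based repeated-measures mixed model with school effects, using all surveys from all consented students in the arm to which their school was randomised.

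If an ANCOVA is kept for presentation, first multiply impute missing surveys within arm from each student's other surveys, so that one missing-data approach applies to all primary outcomes.

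The cost is a change of wording and modest extra programming in Stata, which the plan already uses. No new data are needed.

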### Objectives of the CSC study

The primary objective of the CSC Study is to evaluate an innovative Internet-based prevention program for the prevention and reduction of substance use, anxiety and depressive symptoms, by combining the universal *CLIMATE Schools - Substance Use* program and the *CLIMATE Schools - Mental Health* program.

It is hypothesised that the CSC program will be more effective than; (1) school-based Health and Physical Education as usual, (2) the *CLIMATE Schools - Substance Use* program, and (3) the *CLIMATE Schools - Mental Health* program in relation to the following outcomes:

1) reducing the use and harmful use of alcohol and cannabis

2) reducing overall levels of anxiety and depression

3) increasing knowledge related to alcohol, cannabis anxiety and depression.

Secondary aims include examining the effects of the interventions on alcohol use related harms, self-efficacy to resist peer pressure, general disability, and truancy. The link between personality and substance use, as well as mental health will also be examined.

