### Strengths and limitations

The preventative focus of the CSC study on comorbid substance use and mental health symptoms in young people is a key strength of the study. To date, school prevention programs for anxiety, depression and substance use have mostly been designed to target one disorder at a time, rather than targeting all these common disorders. The development and evaluation of a combined prevention approach to mental health and substance use problems is a critical step in acknowledging the comorbidity of these problems, including common antecedents, as well as influencing policy to improve mental health and wellbeing.

The CSC intervention has been designed to overcome many obstacles and limitations of current school-based preventative programs. First, the program has been specifically designed to link with the curriculum, and is thereby potentially practical, acceptable, and scalable to all schools in Australia. Furthermore, implementation issues that have hindered previous school-based programs have been addressed through the use of innovative online delivery methods, which are designed to increase program fidelity and increase student engagement.

Finally, the study has been powered to allow for comparisons between all four of the intervention conditions, both nationally and within each of the three States for effect sizes as low as .15. Such a large sample will allow for the detection of even small differences between groups. This will enable the investigators to establish the efficacy of the combined program over and above the stand-alone programs, as well as normative substance use and mental health education in Physical Health and Education classes as usual.

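### Within-State power of 80% is stated at an unadjusted 0.05, while the analysis section plans Bonferroni adjustment of unstated scope; if it covers the group contrasts, State-level power is about 57% to 66%

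*Protocol article*

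**What the plan says.** Four places in the protocol article bear on this.

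- **Sample size calculations.** To allow comparisons within a State, "six schools (with at least 100 students) in each of the four intervention groups are required per state". On the power of that design: "This achieves 80 per cent power to detect a standardized between-group mean difference of 0.15 (p = 0.05) in outcomes". No allowance for multiple testing is mentioned. The recruitment target is 28 schools per State, to cover about 10% school dropout.
- **Strengths and limitations.** The article states that "the study has been powered to allow for comparisons between all four of the intervention conditions", nationally and in each of the three States, down to an effect size of 0.15. Four conditions give six pairs at each level.
- **Objectives of the CSC study.** "It is hypothesised that the CSC program will be more effective than" is followed by three comparators: usual education, the substance use programme and the mental health programme. No within-State hypothesis is listed.
- **Statistical analysis.** "For multiple comparisons Bonferroni adjustments will be made". The sentence comes straight after the text on the single-level ANCOVA, which replaces the mixed models when little variance lies between schools or States. Neither the family of comparisons nor its size is given.

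**The concern.** The State-level sample size is built on one alpha and the analysis section appears to prescribe a smaller one. A test with exactly 80% power at 0.05 has less than 80% at any divided alpha, so the State-level claim fails for a Bonferroni family of two or more.

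This matters because State-level power fixes the number of schools per arm and is advertised as a strength of the design. A reader of a null State-level result would take it to come from a test with 80% power for 0.15 SD. If the adjustment applies, that test had materially less, and the null result would be over-read.

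**Working it through.** **Inputs from the article.** Difference 0.15 SD, power 80%, p = 0.05, six schools of at least 100 students per arm per State (600 students), seven measurement occasions, three States, 28 schools recruited per State (28/4 = 7 per arm). Three contrasts come from the objectives. Six pairs come from the claim about all four conditions. Sidedness is not stated; two-sided is assumed.

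**Can the stated 80% be reproduced?** Not from the article, because the intracluster and within-student correlations are not given.

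- A plain comparison of two means with 600 per arm, ignoring clustering and repeated measures, gives 73.8%.
- A slope-difference formula with fixed slopes and seven equally spaced occasions (an assumption) is Φ[(0.15/6) × √(600 × 7 × 4 / (2(1 − ρ))) − 1.96]. It gives 72.6% at ρ = 0.2, 80.0% at about ρ = 0.33 and 90.0% at ρ = 0.5.

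So 80% is attainable but cannot be confirmed. It is taken as given below, and only alpha is changed.

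**Within a State.** 80% at two-sided 0.05 implies a non-centrality of 1.960 + 0.842 = 2.802. With m comparisons:

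- power = Φ(2.802 − z), where z is the normal quantile at 1 − 0.025/m
- detectable difference at 80% power = 0.15 × (z + 0.842)/2.802
- with seven schools per arm, the non-centrality becomes 2.802 × √(7/6) = 3.026

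| Family | z | Power, 6 schools per arm | Detectable difference | Power, 7 schools per arm |
|---|---|---|---|---|
| m = 1 | 1.960 | 80.0% | 0.150 SD | 85.7% |
| m = 2 | 2.241 | 71.2% | 0.165 SD | 78.4% |
| m = 3 (hypothesised contrasts) | 2.394 | 65.8% | 0.173 SD | 73.6% |
| m = 6 (all pairs) | 2.638 | 56.5% | 0.186 SD | 65.1% |

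For scale, restoring 80% would need 6 × ((z + 0.842)/2.802)² retained schools per arm per State: 8.0 for m = 3 and 9.3 for m = 6.

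**Pooled over three States.** There are three times as many schools per arm. With a common effect across States the non-centrality is 2.802 × √3 = 4.853. Power is Φ(4.853 − 1.960) = 99.8% unadjusted, Φ(4.853 − 2.394) = 99.3% for m = 3 and Φ(4.853 − 2.638) = 98.7% for m = 6. It is still 93.8% for m = 54.

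**The case against.** The best reply is that the mismatch touches only part of the trial and depends on a reading of one sentence.

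- **The main comparison is pooled.** The objectives contain no State-level hypothesis, and the sample size section assigns the full sample to the test of the combined programme against the other groups. This stands. A reader might infer that the trial's main hypothesis is underpowered, but the article's figures do not support that: pooled power stays near 99% after adjustment. Nor can the State-level non-centrality be used for a family that mixes national and State-level tests, because the national tests in it keep far higher power.
- **The scope of Bonferroni is not given.** It may cover only the fallback ANCOVA, or pairwise follow-up tests. This also stands, and makes the finding conditional. It does not remove it. If the adjustment excludes the State-level mixed-model contrasts, the text should say so; if it includes them, the 80% is wrong. Detail on families may belong in a separate analysis plan, but alpha, power, adjustment and the claim of adequate power are all stated in the article.
- **Wider multiplicity arguments do not follow.** A reader might go on to claim an inflated family-wise error across primary outcomes. The article names outcome domains but gives no count of tests, and the Bonferroni sentence does not exclude outcomes. A reader might also insist that the three comparators form one all-or-nothing claim needing no adjustment. The numbered list can equally be read as three separate hypotheses, for which Bonferroni is legitimate. Nor is it an error to compare all four conditions, since the design has four groups.

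**Conclusion.** The point holds for within-State comparisons only, and on condition that the Bonferroni adjustment covers the between-group contrasts. The State-level claim of 80% power for 0.15 SD then becomes about 66% for three contrasts or 57% for six pairs. Full retention of the recruited schools does not rescue it for either family.

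The result assumes a two-sided test and the stated 80%. Reading p = 0.05 as one-sided does not help: the non-centrality is 1.645 + 0.842 = 2.487, and power is Φ(2.487 − 2.128) = 64% for m = 3 and Φ(2.487 − 2.394) = 54% for m = 6.

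The statement that the pooled analysis is unaffected also assumes no treatment-by-State heterogeneity. Whether the 80% itself allows enough for school clustering is a separate question that the article's figures cannot settle.

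**What to change.** In the statistical analysis section, state which contrasts the Bonferroni adjustment covers, whether it applies to the mixed models as well as the fallback ANCOVA, and whether it applies to within-State tests. Then take one of two routes:

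- **If within-State contrasts are adjusted:** restate the State-level power or detectable difference at the adjusted alpha in both the sample size and the strengths sections. On the present figures that is about 66% power (or 0.173 SD at 80% power) for three contrasts, or about 57% (or 0.186 SD) for six.
- **If they are not adjusted:** say that within-State contrasts are tested at an unadjusted 0.05. The stated 80% then belongs to the stated test.

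Either route is a change of wording. It needs no more schools and leaves the pooled comparison as it is. The cost is a slightly less favourable State-level figure on the first route, or an explicit admission of unadjusted State-level testing on the second.

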**Methods/design:**

Participants will consist of approximately 8400 students aged 13 to 14-years-old from 84 secondary schools in New South Wales, Western Australia and Queensland, Australia. The schools will be cluster randomised to one of four groups; (i) *CLIMATE Schools Combined* intervention; (ii) *CLIMATE Schools - Substance Use; (iii) CLIMATE Schools - Mental Health*, or (iv) Control (Health and Physical Education as usual).

The primary outcomes of the trial will be the uptake and harmful use of alcohol and other drugs, mental health symptomatology and anxiety, depression and substance use knowledge. Secondary outcomes include substance use related harms, self-efficacy to resist peer pressure, general disability, and truancy. The link between personality and substance use will also be examined.

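### Primary lists differ, no outcome or contrast is decisive, and the 80% within-State power at an undivided 0.05 does not fit the promised Bonferroni adjustment

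*Protocol article*

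**What the plan says.** **Primary outcomes.** The Abstract (Methods/design) states: "The primary outcomes of the trial will be the uptake and harmful use of alcohol and other drugs, mental health symptomatology and anxiety, depression" and goes on to substance use knowledge. Objectives of the CSC study begins its own list with "1) reducing the use and harmful use of alcohol and cannabis", then levels of anxiety and depression, then knowledge. The opening of the Discussion gives a third version: uptake and harmful use of alcohol and other drugs, rates of anxiety and depression, and knowledge.

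**Comparators.** Objectives hypothesises that CSC is better than usual education, than the Substance Use programme and than the Mental Health programme. The three are not ranked, and no decision rule is given.

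**Multiplicity.** Statistical analysis says "For multiple comparisons Bonferroni adjustments will be made". The family is not stated.

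**Power.** Sample size calculations requires "six schools (with at least 100 students) in each of the four intervention groups are required per state" and states: "This achieves 80 per cent power to detect a standardized between-group mean difference of 0.15 (p = 0.05) in outcomes". No multiplicity divisor appears. Strengths and limitations repeats that "the study has been powered to allow for comparisons between all four of the intervention conditions", nationally and within each of the three States.

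**The concern.** There are two linked problems.

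First, the article does not say which result decides the trial. The three lists differ on whether the substance outcome covers cannabis or other drugs generally, on use or uptake, and on levels or rates of symptoms. Within alcohol use alone, the Measures section offers frequency, quantity, drinking to excess, ages of first use and maximum drinks. With several primary measures, three comparators each and no family for the adjustment, the threshold for a single test could be 0.0167 (three arms within an outcome), 0.0083 (all six pairs within an outcome) or 0.0019 (27 tests). A borderline result would be called either way depending on the choice.

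Second, the power statement and the analysis statement do not fit together. The sample size assumes each comparison is tested at 0.05, while the analysis section says multiple comparisons will be adjusted. If the adjustment reaches the powered within-State comparisons, the stated 80% does not hold for them.

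**Working it through.** **1. The plan's own figure.** Inputs from Sample size calculations: 6 schools of 100 students per arm per State, seven occasions, standardized difference 0.15, 80% power, p = 0.05. Sidedness is not stated; two-sided is assumed. The article gives no within-student correlation r, so r was varied. For a slope comparison:

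schools per arm = 2(1 − r)(1.96 + 0.84)² / (100 × 7 × Var(T) × (0.15/T_end)²)

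With equally spaced occasions T = 0 to 6, Var(T) = 4 and T_end = 6. At r = 0.35 this gives 2 × 0.65 × 7.849 / 1.75 = 5.83, so 6 schools (power 81.1%). At r = 0.33, six schools give 79.9%. With assumed calendar spacing (0, 6, 12, 13, 18, 24, 30 months), r = 0.40 gives 80.3%. The 80% is therefore attainable, but it rests on an unstated input. It is taken as correct below.

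**2. Counting the primary tests.** From Objectives: use and harmful use, each of alcohol and cannabis (4); anxiety and depression (2); knowledge scales for alcohol, cannabis and anxiety/depression (3). That is 9 measures × 3 contrasts = 27 tests. The article does not give this count.

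**3. Family-wise error when nothing works.** Simulation with 200,000 draws: four arm means per outcome, contrasts z = (CSC − other)/√2 so that they share the CSC arm, and a common correlation between outcomes of 0.5 to 0 (assumed). Each range runs from correlation 0.5 to 0.

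| Rule, 9 outcomes × 3 contrasts | Any false result | Favouring CSC only |
|---|---|---|
| No adjustment | 56–70% | 29–44% |
| 0.05/3 within each outcome | 26–34% | 13–18% |
| 0.05/27 over all tests | 4–5% | about 2% |

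Check of the 34%: at 0.05/3 the chance of any false result among the three contrasts of one outcome is about 0.045, and 1 − (1 − 0.045)⁹ ≈ 0.34. With 7 to 10 measures, the 0.05/3 row runs from 22% (7 measures, correlation 0.5) to 37% (10 measures, correlation 0).

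**4. If CSC must beat all three arms.** With each contrast at 0.05 and no effect anywhere, a false claim on any of nine outcomes has probability 1.2–1.4%. That is not the worst case. If CSC clearly beats two arms but only equals the third, each outcome errs at up to 0.025, and over nine independent outcomes 1 − 0.975⁹ = 20%.

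**5. Power at a divided alpha.** 80% at two-sided 0.05 means an expected z of 1.960 + 0.842 = 2.802 within a State. Nationally there are three times as many schools, giving 2.802 × √3 = 4.852. Power = Φ(expected z − critical z).

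| Alpha | Critical z | Within State | National |
|---|---|---|---|
| 0.05 | 1.960 | 80% | 99.8% |
| 0.05/3 | 2.394 | 66% | 99% |
| 0.05/6 | 2.638 | 56% | 99% |
| 0.05/27 | 3.113 | 38% | 96% |

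**6. Power of the joint claim.** For all three contrasts on one outcome (correlation 0.5 from the shared arm), within-State power is 61% at 0.05 and 42% at 0.05/3. Nationally it is about 99% and 98%.

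**The case against.** The strongest reply is that the adjustment family, hierarchy and alpha split are commonly left to an analysis plan, which is not shown here. That stands: an undefined family alone would not be a finding. It does not answer the power point, because no divisor that the analysis plan could choose for those comparisons leaves the published within-State 80% true. Nor does it explain three differing primary lists in one article.

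Some stronger readings are tempting but not supported:

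- **That a false primary success is likely.** Only the unadjusted case passes 50%, and the article promises Bonferroni. Every adjusted reading examined stays well below that.
- **That there are 54 tests, because growth terms double the count.** Statistical analysis presents growth terms as describing the size of follow-up effects, not as a second decisive test.
- **That a full correction removes the trial's power.** It does so within States only. The hypotheses are not State-specific, and national power stays at about 96% at 0.05/27.
- **That the adjustment covers only the ANCOVA fallback.** The sentence follows that fallback, but the next one, on effect sizes and intervals, is plainly general, so its position proves little.
- **That a knowledge gain alone would be a false positive.** A real gain in knowledge is a real effect. Knowledge and cannabis use are stated primary aims, and moving them to secondary would change the trial rather than correct an error.

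Objections also joins the three comparators with *and*, which permits an all-three rule with very low error when nothing works. No decision rule adopts it, and step 4 shows that it would still need control across outcomes.

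**Conclusion.** The point holds in a limited form. The article gives differing primary lists with no decisive outcome or contrast. Bonferroni over the arms within each outcome would leave a family-wise error of about 26–34% over nine measures, or 13–18% counting only results favouring CSC. This assumes nine measures, outcome correlation between 0.5 and 0, and any single contrast counting as success.

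Separately, the 80% within-State power is inconsistent with Bonferroni applied to those comparisons: 66%, 56% or 38% for divisors of 3, 6 or 27. National power is about 96% or more in each case. That figure assumes the stated 80% is right, a two-sided test, and the same effect and variance across three times as many schools.

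This should be corrected, but it does not threaten the main national comparison.

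**What to change.** 1. Reconcile the Abstract, Objectives and Discussion into one primary list, with a named measure and time point for each primary domain. Keep the sponsor's stated aims, including cannabis use and knowledge.
2. State whether CSC must beat all three comparators for a claim on an outcome. If so, drop the correction across arms and apply Holm across the primary outcomes. If not, apply Holm or Bonferroni over the full outcome-by-contrast family. Use the same rule whether the outcome is analysed by the hierarchical models or by ANCOVA.
3. Restate the power in Sample size calculations and in Strengths and limitations at the resulting alpha, with the national comparison as confirmatory and the within-State comparisons labelled as lower-powered or exploratory.

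This is wording only, made before outcome data are seen; no further schools or data are needed. It has two costs. The stated within-State power becomes less favourable. Requiring all three contrasts also lowers the power of the joint claim: for example, 42% within a State at 0.05/3, the first Holm step if there were three primary outcomes.
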